## Abstract

**Background:**

Hemolysis, elevated liver enzymes, and low platelets (HELLP) syndrome is one of the most severe forms of preeclampsia and aggravates both maternal and perinatal prognosis. The systematic review available in Cochrane Library compared corticosteroid (dexamethasone, betamethasone, or prednisolone) given during pregnancy, just after delivery or in the postnatal period, or both before and after birth, with placebo or no treatment. Those receiving steroids showed significantly greater improvement in platelet counts which was greater for those receiving dexamethasone than those receiving betamethasone. There was no clear evidence of any effect of corticosteroids on substantive clinical outcomes. These benefits appear to be greater in Class I HELLP syndrome.

**Objectives:**

To determine the effectiveness of dexamethasone for accelerating postpartum recovery in patients with Class I HELLP syndrome in a multicenter randomized controlled trial.

**Methods/Design:**

The study is a triple blind randomized controlled trial including women with class I HELLP syndrome, and exclusion criteria were dexamethasone use in the last 15 days before diagnosis of HELLP syndrome; chronic use of corticosteroids; chronic diseases that alter laboratory parameters of HELLP Syndrome, such as chronic liver disease or purpura, patients unable to consent (coma or critical clinical condition) and without accompanying persons that may consent to study participation.

Eligible patients will be invited to participate and those who agree will be included in the study and receive placebo or dexamethasone according to a random list of numbers and subjects will receive the study medication every 12 hours for two days.

During the study the women will be subject to strict control of blood pressure and urine output. Laboratory tests will be performed at regular intervals during treatment and 24 hours and 48 hours after its suspension. If worsening of clinical or laboratory variables is observed, a rescue scheme of dexamethasone will be administrated. This proposal has already obtained approval of the local Institutional Review Board of the coordinating center (IMIP, Recife, Brazil), all other participating centers and of the National Council for Ethics in Research (CONEP) of the Brazilian Ministry of Health.

**Trial Registration:**

Clinical Trials Register under the number
NCT00711841.

A study carried out in a tertiary center in Brazil in 2008, failed to confirm any significant effect of the use of dexamethasone on the clinical and laboratory parameters of HELLP Syndrome in postpartum period. There was no difference in the evolution of laboratory or clinical parameters, frequency of maternal complications, need for rescue scheme, or length of hospital stay among patients who received dexamethasone and those who received placebo
[15].

The systematic review available in the Cochrane Library identified 11 randomized controlled trials involving 550 women that compared corticosteroid (dexamethasone, betamethasone, or prednisolone) given during pregnancy, just after delivery or in the postnatal period, or both before and after birth, with placebo or no treatment. There was no clear evidence of any effect of corticosteroids on substantive clinical outcomes. Those receiving steroids showed significantly greater improvement in platelet counts which was greater for those receiving dexamethasone than those receiving betamethasone. The authors concluded that evidences are insufficient to demonstrate substantive improvement of clinical outcomes among women receiving steroids for management of HELLP syndrome. Notwithstanding, they suggest that the use of corticosteroids may be justified in clinical situations in which increased rate of recovery in platelet count is considered clinically worthwhile
[16].

HELLP syndrome is a rare disease and its more severe forms are even rarer. To evaluate only the most severely ill patients, who are possibly those who would most benefit from corticosteroid therapy as shown in the study carried out by Fonseca et al.
[14], various centers would have to be involved to achieve an adequate sample size with sufficient power to define infrequent outcomes such as death.

The overall objective of this study is to determine the effectiveness of dexamethasone to accelerate the postpartum recovery of patients with class I HELLP syndrome.

### Objectives and hypothesis

The overall objective is to determine the effectiveness of dexamethasone for accelerating postpartum recovery in patients with Class I HELLP syndrome in a multicenter randomized controlled trial.

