#### Primary outcome

•Frequency of composite maternal morbidity (acute pulmonary edema, eclampsia, bleeding manifestations, shock, coma, renal failure, liver failure, DIC, blood transfusion or death).

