#### Secondary outcomes

•Laboratory parameters during and after treatment (hemoglobin, platelets, LDH, transaminases and bilirubin).

•Diuresis during and after treatment.

•Frequency of maternal complications: acute pulmonary edema, bleeding, acute renal failure and death.

•Need for rescue therapy regimen during the observation period.

•Time elapsed between the first dose of medication (dexamethasone or placebo) and egress (discharge or death).

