#### Main hypothesis

In patients with class I HELLP Syndrome receiving dexamethasone, in comparison with placebo:

•The frequency of composite maternal morbidity is lower.

•Hemoglobin and platelets levels are greater while LDH, transaminases and bilirubin levels are lower.

•Better diuresis is achieved.

•Maternal complications are less frequent.

•There is less need for rescue therapy regimen during the observation period.

•Time elapsed between the first dose of medication and hospital discharge is lower.

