### Procedures for selecting participants and randomization

Eligible patients will be invited to participate and those who agree will be included in the study and receive placebo or dexamethasone according to a random list of numbers generated by the Random Allocation Software Ispharan Iran, version 1.0. This list of randomization will be provided by the statistician to the pharmacist who will be responsible for preparing the packages containing either the dexamethasone or placebo, both in an identical presentation, with the identification number of list labeled. This procedure will be followed in order to guarantee the concealment of allocation of patients in both arms. Considering dexamethasone has no important immediate identifiable effects, either patients and medical staff should be blind of the intervention condition in each case. Study medication and placebo, after delivered by the pharmaceutical industry to the pharmacy of the coordinating center, will be packed as previously described and according the random list. The pharmacy will be responsible for sending sets of 5 or 10 packages to each center depending on their performance on patients’ enrollment. The subjects will receive the study medication every 12 hours for two days.

During the observation period the women will be subject to strict control of blood pressure and urine output (diuresis evaluated spontaneous or urinary catheter). Laboratory tests will be performed at regular intervals of 24 hours (blood count, coagulation, renal and hepatic function) during treatment and 24 hours and 48 hours after its suspension. If investigators observe worsening of clinical or laboratory variables the study protocol will be interrupted and dexamethasone will be administrated. The same will be done if after the end of the two days the clinical situation deteriorates or does not improve. The patient will be considered as belonging to the group that she was originally randomized to, independent of later use of dexamethasone (type analysis intention to treat), recording such cases the need for "rescue therapy".

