### Main outcomes

•Hypertensive disorders of pregnancy: defined according to the National High Blood Pressure Education Program Working Group on High Blood Pressure in Pregnancy
[17].

•Maternal complications: any of these conditions: acute pulmonary edema, eclampsia, bleeding manifestations, shock, renal failure, coma, liver failure and blood transfusion.

•Composite maternal morbidity: presence of one or more of the following findings: acute pulmonary edema, eclampsia, bleeding manifestations, shock, coma, renal failure, liver failure, DIC, blood transfusion and death.

•HELLP syndrome: defined according to the criteria defined by Sibai
[1]: 1. Hemolysis: characterized as the presence of abnormal peripheral blood smear (schystocytosis, anisocytosis, echinocytosis, poikilocytosis) associated with increased serum total bilirubin (> 1.2 mg%) or LDH increased (> 600 U/l); 2. Increased liver enzymes: when the serum AST is greater than 70 U/l or serum lactate dehydrogenase was higher than 600 U/l; 3. Thrombocytopenia: considered when the platelet count is less than 100.000/mm^3^.

•Rescue corticosteroid scheme: use of ampoules of intravenous dexamethasone in patients who had no improvement in laboratory tests or worsened in the course of the drug and therefore had the outline of the study (dexamethasone or placebo) suspended. Will also be adopted in patients who, after two days persisted with very altered laboratory tests.

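### The overall objective is faster recovery, but the primary outcome and sample size concern whether morbidity occurs; recovery speed is covered only indirectly, by secondary outcomes, one of which counts an early death as a short time

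*Protocol article*

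**What the plan says.** The Abstract (Objectives), the end of the Introduction and the section Objectives and hypothesis all give the same overall aim. In the last of these: "The overall objective is to determine the effectiveness of dexamethasone for accelerating postpartum recovery in patients with Class I HELLP syndrome".

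Under Primary outcome the measure is "Frequency of composite maternal morbidity". Main outcomes defines it as "presence of one or more of the following findings: acute pulmonary edema, eclampsia, bleeding manifestations, shock, coma, renal failure, liver failure, DIC", followed by blood transfusion and death. Sample size calculation rests on this proportion only: 50% with placebo, 35% with dexamethasone, 80% power, 5% alpha, 364 women, raised to 400.

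Recovery appears under Secondary outcomes in two main forms. One is "Laboratory parameters during and after treatment (hemoglobin, platelets, LDH, transaminases and bilirubin"), with diuresis over the same period. The other is "Time elapsed between the first dose of medication (dexamethasone or placebo) and egress (discharge or death"). Dependent variables repeats both. Main hypothesis expects higher haemoglobin and platelets, lower LDH, transaminases and bilirubin, and "Time elapsed between the first dose of medication and hospital discharge is lower".

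On timing, Procedures for selecting participants and randomization says: "Laboratory tests will be performed at regular intervals of 24 hours" during the two days of treatment, then 24 and 48 hours after it stops.

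**The concern.** Whether a complication ever occurs and how quickly a woman recovers are different quantities. The Introduction treats them separately: it reports recovery time, hospital stay and complications of the largest earlier trial as distinct results. It also motivates the restriction to Class I disease partly by faster platelet recovery and shorter stay in that subgroup. A reader who takes the overall objective at its word will look to the primary result for the answer on speed, and it is not there.

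The one outcome measured in time has a problem of its own. Because it ends at discharge or death, a woman who dies soon after the first dose has a short time, and the hypothesis is that shorter is better. The hypothesis itself is worded for discharge only, so outcome and hypothesis do not describe the same variable.

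At stake is the conclusion. A claim of accelerated recovery could be attached to a result that does not measure it, or to a time to egress shortened by deaths.

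**Working it through.** **1. What the sample size is built for.** Inputs from Sample size calculation: p1 = 0.50, p2 = 0.35, 80% power, alpha 5%; two-sided from Data analysis plan. Allocation 1:1 is assumed, as the article does not state it.

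- Mean proportion: (0.50 + 0.35)/2 = 0.425.
- Without continuity correction: n0 = [1.9600·√(2·0.425·0.575) + 0.8416·√(0.50·0.50 + 0.35·0.65)]² / 0.15² = (1.3702 + 0.5816)² / 0.0225 = 169.3 per arm, so 170 per arm and 340 in total.
- With continuity correction: n = (n0/4)·[1 + √(1 + 4/(n0·0.15))]² = 182.4 per arm. Rounded up this is 183 per arm (366 in total); rounded to nearest it is 182 per arm (364).
- Losses: 364/(1 − 0.09) = 400.

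The plan's 364 is therefore reproduced to within 2 women by a two-sided comparison of two proportions. No recovery-time assumption enters it.

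**2. Objective and outcomes side by side.**

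- Overall objective: acceleration of recovery, a rate.
- Primary outcome: presence of at least one listed event, with no time element in the definition.
- Laboratory secondary outcomes: levels during and after treatment. No recovery event or threshold is defined in the article.
- Timed secondary outcome: first dose to discharge or death.
- Matching hypothesis: first dose to discharge.

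**3. What death does to time to egress.** Let T be the recorded time. A woman who dies at time d has T = d. Under a rank comparison such as Mann–Whitney, a d earlier than all discharges takes the most favourable ranks. If treatment prevented such a death, a short T would be replaced by a longer one and the treated arm would look slower. The outcome can thus move against a real benefit. The article gives no death rate, so the size cannot be calculated.

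**4. Whether a timed comparison is feasible.** Schoenfeld, 1:1, two-sided 5%, 80% power: detectable HR = exp[2·(1.9600 + 0.8416)/√events].

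- Time to discharge, assuming every woman is discharged alive: 364 events give exp(5.603/19.08) = 1.34; 400 events give exp(5.603/20) = 1.32.
- Time to laboratory recovery, with assumed numbers recovering in the testing window: 380 give 1.33, 300 give 1.38, 200 give 1.49.

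Taking treatment to end at about 48 hours, the scheduled tests fall at about 24, 48, 72 and 96 hours. That supports a time to recovery in 24-hour steps. The hazard ratios treat time as continuous and the event counts are assumptions, so they show feasibility and nothing more.

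**The case against.** The strongest reply is that the plan does address speed. Between randomised arms, higher platelets and lower LDH at fixed times are an accepted sign of faster recovery, and this comparison is reasonably sensitive: with 182 per arm, 80% power for a difference of 2.8016·√(2/182) = 0.29 SD. Time from first dose is also a listed outcome with a directional hypothesis. In addition, the specific objectives and the first hypothesis make lower composite morbidity an explicit question, and the Introduction argues for a multicentre trial by reference to infrequent outcomes such as death. A clinical primary outcome follows from that argument. All of this stands.

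A reader might therefore be tempted by a stronger statement: that the trial cannot answer its stated question, or that none of its data bear on speed. The documents do not support either. The primary outcome answers the morbidity question, and the secondary outcomes give indirect evidence on recovery.

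It is also fair that death is not hidden, since it is counted in the composite and among the complications. Further, a condensed article may leave analysis methods and recovery thresholds to the full protocol or SAP, so the missing threshold is not in itself a fault. That does not excuse the mismatch: the objective, the outcomes and the hypotheses are all written out, and they disagree.

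Finally, a platelet threshold is only one choice. It sets aside haemolysis and liver enzymes, and transfusion or rescue dexamethasone can affect it. This is a reason to keep such an outcome secondary.

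**Conclusion.** The concern holds as a misalignment. The overall objective, stated in three places, is about speed; the primary outcome and the 364/400 women are about occurrence. Recovery is reached only through secondary outcomes that were not separately powered, and the single timed outcome treats death as equivalent to discharge, contrary to its own hypothesis.

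It should be corrected, but it does not threaten the primary analysis or require a different sample size. Its weight lies in what may be concluded at the end. No numerical bias can be given, because the article states neither a death rate nor a recovery-time distribution. The hazard ratios of about 1.32 to 1.49 rest on assumed event counts and 1:1 allocation, and they measure what a timed analysis could detect, not the harm done by the present wording.

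**What to change.** 1. Keep the primary outcome and the 364/400 sample size.
2. In the Abstract, the Introduction and Objectives and hypothesis, reword the overall objective to reduction of composite maternal morbidity, with faster recovery as a named secondary objective. Reconsider the word postpartum at the same time, because Eligibility criteria admits women antepartum as well.
3. Replace time to egress by time from first dose to discharge alive, with death as a competing event or counted as never discharged, and word the outcome and its hypothesis identically.
4. Add a secondary outcome of time from first dose to laboratory recovery, using the 24-hourly tests already scheduled. One reasonable definition is a platelet count at or above 100,000/mm³, the limit in the article's own HELLP definition, with death counted as not recovered. Analyse women given rescue dexamethasone in their randomised group, as the article already states, and record transfusions.
5. Tie any conclusion of faster recovery to items 3 and 4.

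The cost is wording in three places, one redefined outcome and one added secondary analysis, with no new tests. The laboratory outcome resolves time only to 24 hours and has no separate powering.

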#### Specific objectives

Analyzing patients with class I HELLP Syndrome randomized to receive dexamethasone or placebo, the specific objectives are to compare:

#### Primary outcome

•Frequency of composite maternal morbidity (acute pulmonary edema, eclampsia, bleeding manifestations, shock, coma, renal failure, liver failure, DIC, blood transfusion or death).

#### Secondary outcomes

•Laboratory parameters during and after treatment (hemoglobin, platelets, LDH, transaminases and bilirubin).

•Diuresis during and after treatment.

•Frequency of maternal complications: acute pulmonary edema, bleeding, acute renal failure and death.

•Need for rescue therapy regimen during the observation period.

•Time elapsed between the first dose of medication (dexamethasone or placebo) and egress (discharge or death).

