#### Dependent variables

composite maternal morbidity, laboratory parameters during and after treatment (hemoglobin, platelet count, LDH, transaminases and bilirubin), diuresis during and after treatment, maternal complications, need for rescue therapy regimen, time elapsed between the first dose of medication (dexamethasone or placebo) and egress (discharge or death).

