#### Data analysis plan

The data analysis will be performed using the public domain software Epi Info version 7 (Centers for Disease Control and Prevention, Atlanta, GA), or the newest available version under the intention to treat principle. The statistician and the investigators will remain blind to the treatment groups until the tables will be prepared and the analysis concluded. The approach for analysis will be that showed in Figure 
1 using an intention-to-treat strategy and following the correspondent recommendations from the CONSORT statement
[19]. The characteristics of the participants in each group will be compared with Student’s *t* test for continuous variables with normal distribution and Mann–Whitney U test for discrete and ordinal variables or those with non-normal distribution. Categorical variables will be compared with Pearson’s χ^2^ test or Fisher’s exact test, as appropriate. P values for all tests will be two tailed at a 5% level of significance. Risk ratios and their 95% confidence intervals will be calculated as a measure of relative risk. The number needed to treat (NNT) and its 95% confidence interval will be calculated for the outcomes in which a beneficial effect of dexamethasone treatment is achieved, using the EBM calculator [
http://moosenose.com/EBCalculator.htm]; in case of adverse effects the number needed to harm (NNH) and its 95% confidence will also be calculated.

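### Time to egress stops the same clock for discharge and for death, so an early death scores as a fast recovery and the outcome does not match its own hypothesis (secondary outcome; should be fixed)

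*Protocol article*

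**What the plan says.** The protocol article describes this outcome in three places.

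- Secondary outcomes: "Time elapsed between the first dose of medication (dexamethasone or placebo) and egress (discharge or death").
- Dependent variables, in the same terms: "time elapsed between the first dose of medication (dexamethasone or placebo) and egress (discharge or death").
- Main hypothesis, for dexamethasone compared with placebo: "Time elapsed between the first dose of medication and hospital discharge is lower". Death is not mentioned here.

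The Introduction gives the overall objective as "to determine the effectiveness of dexamethasone to accelerate the postpartum recovery of patients with class I HELLP syndrome". Death is also counted in the primary composite, which ends "renal failure, liver failure, DIC, blood transfusion or death", and in another secondary outcome: "Frequency of maternal complications: acute pulmonary edema, bleeding, acute renal failure and death".

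The Data analysis plan names Student's t test for normally distributed continuous variables and the Mann–Whitney "U test for discrete and ordinal variables or those with non-normal distribution". That sentence is about comparing participants' characteristics, but the article names no other test for a continuous measure. No section gives a rule that treats a death differently from a discharge in this outcome.

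**The concern.** Discharge and death are opposite results, but here each ends the measurement in the same way and a smaller value is declared better. A death on day 1 receives close to the best possible score. If deaths come earlier than typical discharges, a drug that prevents deaths is penalised on this outcome and a drug that causes them is rewarded.

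Separately, and whatever the mortality, the outcome (discharge or death) is not the quantity in the hypothesis (discharge).

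This is the only outcome in the article that is expressed as a time to an event, in a trial whose stated purpose is faster recovery. A reader will naturally turn to it for that purpose.

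A smaller point is that the clock starts at the first dose although the analysis is by intention to treat. A randomised woman who is never dosed has no value.

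**Working it through.** **1. Inputs.** The article gives no mortality, time of death or length of stay, and no target difference for this outcome. Its only sample-size figure is 364, for the primary composite at 50% against 35%, 80% power and 5% alpha. Equal allocation is assumed here.

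- Without continuity correction: n = [1.96·√(2·0.425·0.575) + 0.8416·√(0.25 + 0.2275)]² / 0.15² = 169.3 per arm.
- With continuity correction: (169.3/4)·[1 + √(1 + 4/(169.3·0.15))]² = 182.4 per arm. This gives 364 in total if rounded down (366 if rounded up).

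The stated figure reproduces. It does not bear on the defect; it only supplies the 182 per arm used below.

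Assumptions not in the article: discharge times lognormal with median 7 days and log SD 0.5; death times exponential with mean 2 days, and 10 days as a late-death check; two-sided Mann–Whitney test at 5%.

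**2. Direction, by arithmetic.** Take identical discharge times in both arms, mortality pP on placebo and pD on dexamethasone, and let q be the probability that a death occurs earlier than another woman's discharge. The probability that a placebo patient has the longer time is

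(1−pP)(1−pD)/2 + pP·pD/2 + pP(1−pD)(1−q) + (1−pP)pD·q = 0.5 + (pP − pD)(0.5 − q).

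Above 0.5 favours dexamethasone. Ranking death worst is the same as setting q = 0.

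| Mortality, placebo vs dexamethasone | Deaths | q | As written | Death ranked worst |
|---|---|---|---|---|
| 8% vs 3% | mean 2 days | 0.94 | 0.5 + 0.05·(−0.44) = 0.478 | 0.5 + 0.05·0.5 = 0.525 |
| 8% vs 3% | mean 10 days | 0.51 | 0.5 + 0.05·(−0.01) ≈ 0.499 | 0.525 |
| 3% vs 10% | mean 2 days | 0.94 | 0.5 − 0.07·(−0.44) = 0.531 | 0.5 − 0.07·0.5 = 0.465 |

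The sign is wrong whenever q exceeds 0.5, that is, when deaths tend to precede discharges. It is close to neutral when deaths come at about the usual discharge time.

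**3. Power when the stay is truly 13% shorter** (3,000 simulated trials per row; simulation error about 1 percentage point).

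| Mortality, placebo vs dexamethasone | Deaths | As written | Death ranked worst |
|---|---|---|---|
| 8% vs 3% | mean 2 days | about 38% | about 88% |
| 2% vs 1% | mean 2 days | 68% | 78% |
| 1% vs 0.5% | mean 2 days | 70% | 74% |
| 3% vs 3% | mean 2 days | about 68% | about 68% |
| 8% vs 3% | mean 10 days | 66% | 89% |

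At 8% vs 3%, a comparison of survivors alone has about 71% power. So of the gap from 38% to 88%, the part from 38% to 71% is information on stay lost by mixing deaths in as short stays. The part from 71% to 88% is credit for lower mortality.

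**4. False benefit.** With no effect on discharge time and mortality of 3% on placebo and 10% on dexamethasone (deaths at mean 2 days), about 17% of trials show a significant benefit of dexamethasone as written. The nominal rate is 2.5%. With death ranked worst it is about 0.1%.

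**The case against.** The strongest reply concerns weight, not correctness. This is the last of five secondary outcomes. The primary test and the sample size do not use it, and death is compared both in the primary composite and among the complications. An excess of deaths would therefore be reported beside a misleadingly short time to egress. A reader might infer that the trial could hide a mortality harm; the article does not support that. What remains is that separate reporting of deaths does not correct this outcome's own estimate or p-value.

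A reader might also infer that this is the trial's only measure of speed of recovery. It is not: platelets, LDH, transaminases, bilirubin and diuresis are followed during and after treatment, with laboratory tests every 24 hours during treatment and at 24 and 48 hours after it. It is only the sole time-to-event outcome.

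The size is open to challenge, and this part of the reply stands. The Introduction groups death with "sufficient power to define infrequent outcomes such as death", so large differences in mortality may be unrealistic. At 2% vs 1% or below the loss is modest. With later deaths the reversal disappears, although some power is still lost. Even at 8% vs 3%, the two Mann–Whitney probabilities (0.478 and 0.525) each lie within one standard error (0.030) of 0.5, so a single trial would rarely show the contrast.

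The never-dosed point is minor. Treatment is short and given in hospital, and nothing suggests that such women would be common.

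It could be said that handling of deaths belongs in an analysis plan that is not shown. The choice of method may. The definition, however, is fixed in the article, and so is its mismatch with the hypothesis.

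**Conclusion.** The outcome is wrong as written. Death and discharge end the same clock, a shorter time is called better, and the hypothesis names a different endpoint. The mismatch in wording holds at any mortality. The bias towards the arm with more deaths holds only if deaths tend to come before the usual discharge and mortality differs between arms.

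Its size cannot be fixed from the article. Under the stated assumptions it runs from a few percentage points of power (70% vs 74% at 1% vs 0.5% mortality) to a large loss (about 38% vs 88% at 8% vs 3%), part of the latter being mortality credit. In the harmful direction, about 17% of trials would show a false benefit at 3% vs 10%.

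This should be fixed, but it is not critical: the outcome is secondary, deaths are compared elsewhere, and the primary conclusion is untouched.

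**What to change.** Define the outcome as time from randomisation to discharge alive, and word it identically under Secondary outcomes, Main hypothesis and Dependent variables. State that an in-hospital death is never counted as an early discharge. In the Mann–Whitney test that the article names, give it the worst rank (longer than any observed stay). If the analysis plan prefers, treat it as a competing event instead. The two answer somewhat different questions, so choose one and record it before unblinding.

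Comparing survivors alone is not a substitute, because it drops women on the basis of an event after randomisation.

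Starting the clock at randomisation also gives a value to any randomised woman who is never dosed.

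The cost is rewording: no extra patients, no new outcome data beyond the date and time of randomisation, and no change to care. The downside is that with death ranked worst the result combines stay and mortality, so it should be read beside the deaths, which the article already plans to compare separately.
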